## Abstract

**Background:**

Cardiovascular disease and cancer are leading causes of mortality for people with a history of alcohol or other substance use disorders. These chronic diseases share the same four primary behavioural risk factors i.e. excessive alcohol use, smoking, low intake of fruit and vegetables and physical inactivity. In addition to addressing problematic alcohol use, there is the potential for substance abuse treatment services to also address these other behaviours. Healthy Recovery is an 8-session group-based intervention that targets these multiple behavioural health risk factors and was developed specifically for people attending substance abuse treatment. This protocol describes a Cancer Institute NSW funded study that assesses the effectiveness of delivering Healthy Recovery for people who are attending residential alcohol and other substance abuse treatment.

**Methods/Design:**

The study uses a stepped wedge randomised controlled design, where randomisation occurs at the service level. Participants will be recruited from residential rehabilitation programs provided by The Australian Salvation Army. All participants who (1) currently smoke tobacco and (2) are expected to be in the residential program for the duration of the 5-week intervention will be asked to participate in the study. Those participants residing at the facilities assigned to the treatment condition will complete Healthy Recovery. The intervention is manual guided and will be delivered over a 5-week period, with participants attending 8 group sessions. All participants will continue to complete The Salvation Army residential program, a predominantly 12-step based, modified therapeutic community. Participants in the control condition will complete treatment as usual. Research staff blind to treatment allocation will complete the primary and secondary outcome assessments at baseline and then at weeks 8, 20 and 32 weeks post intervention.

**Discussion:**

This study will provide comprehensive data on the effect of delivering a healthy lifestyle intervention (i.e. Healthy Recovery) within a residential substance abuse setting. If shown to be effective, this intervention can be disseminated within other residential substance abuse programs.

**Trial registration:**

Australian and New Zealand Clinical Trials Register (ANZCTR): ACTRN12615000165583. Registered 19^th^ February 2015.

## Background

Cardiovascular disease and cancer are leading causes of mortality for people with a history of alcohol or other substance abuse problems [1,2]. The high incidence of chronic diseases is largely the result of this population engaging in multiple unhealthy lifestyle behaviours. In addition to their use of alcohol and illicit substances, people with a history of alcohol or other substance abuse problems commonly demonstrate high rates of smoking, poor dietary behaviours, and low levels of physical activity.

### Smoking

Rates of smoking are much higher for people with alcohol or other substance abuse problems compared to people in the general population [3-5]. Participants with substance abuse problems also tend to smoke substantially more cigarettes each day and demonstrate a higher rate of nicotine dependence [6]. In alcohol dependent populations, tobacco-related causes of death account for a higher rate of mortality than alcohol-related causes of death [7].

### Diet

People with a history of substance abuse problems also tend to have very poor dietary habits. Whilst they are in active addiction, malnutrition occurs in 5-30% of cases [8]. However, once they access residential treatment they are more likely to overeat, and consume energy-dense, nutrient-poor diets [4]. It is very common for people accessing treatment to report concerns with unhealthy eating patterns, unhealthy weight gain and development of obesity [9], with weight gains of approximately 3 kilograms over 12 weeks common. Both neurobiological theories of obesity [10] and interviews with recovering substance abusers [9] suggest that energy-dense diets are used as a substitute for alcohol or drug use during recovery [10].

### Physical activity

Surveys of participants in treatment settings indicate that participants have positive attitudes towards physical exercise and report the desire to increase their physical activity as a way to manage their weight gain [9]. However, less than half of all participants in treatment regularly engage in recommended levels of physical activity [4]. Exercise has been suggested as a potentially important clinical adjunct to addiction treatment, although research in this field is still in its infancy [11].

Whilst residential substance abuse treatment services provide a stable environment to target these multiple health risk behaviours, these services tend to focus almost solely on the person’s alcohol and illicit substance abuse problems. There is an opportunity for substance abuse services to also address smoking [5,12] and other risk behaviours [4] more systematically and as part of routine care.

### Multiple health behaviour change

There is “incontrovertible evidence supporting the medical and economic benefits of prevention” for cardiovascular disease and cancer [13]. It is well established that behavioural interventions focused on preventing these diseases should target smoking, poor diet, alcohol misuse and physical inactivity [14]. Although these diseases are caused by multiple health risk behaviours, historically intervention research has focused on only a single behaviour. An emerging area of preventive health research is focused on examining the effectiveness of delivering interventions that address multiple health risk behaviours (i.e. an intervention that targets both alcohol use and smoking; [15-17]). A limitation with the multiple health risk behaviour change literature is that it has focused mostly on people from the general population. It is essential that multiple health risk behaviour change interventions are developed and trialled with the most marginalised populations, as these groups tend to demonstrate the highest rates of risks (e.g. [4]), have much poorer health outcomes, and have higher rates of mortality (e.g. [1]).

There have been repeated calls to address smoking cessation [5,7], improve diet and nutrition [9], and promote physical activity in substance abuse treatment [11,18]. Yet, most residential services in Australia, and internationally, do not address these behaviours in a meaningful way [19,20]. The reluctance to address multiple health behaviours is largely the result of long standing beliefs of service providers that attempting to make too many lifestyle changes will undermine the person’s recovery from addiction. This view has particularly been expressed in terms of smoking cessation [20]. However, it is at odds with the increasing empirical support for the use of multiple behaviour change interventions [16,21]. For example, a meta-analytic review of smoking cessation interventions suggests that addressing smoking during alcohol and other substance abuse treatment actually enhances longer-term sobriety outcomes [22]. The failure to address multiple risk behaviours also neglects the significant opportunity that substance abuse services could play in helping to reduce the incidence of chronic disease for this marginalised population. Previous research has not examined the implementation of multi-focused, healthy lifestyle interventions for people with alcohol and other substance use disorders.

### The current study

The current project will be conducted at residential alcohol and other drug treatment services provided by The Salvation Army. The sites are located in New South Wales (Dooralong, Sydney, Blue Mountains) and the Australian Capital Territory (Canberra), Australia. These centres provide a modified therapeutic community that is up to 10-months in duration. The study will aim to examine the effectiveness of ‘adding’ a healthy lifestyle group program (i.e. Healthy Recovery) to treatment as usual. Adapted from the work of Baker et al. [23,24], Healthy Recovery is an 8-session group based program that aims to help participants to reduce their smoking, increase their intake of fruit and vegetables, and increase their level of physical activity. The study will be conducted as a stepped wedge randomised controlled trial, in which participants attending sites allocated to the treatment condition will complete Healthy Recovery, in addition to treatment as usual. Participants attending sites allocated to the control condition will continue to complete treatment as usual. It is expected that participants completing Healthy Recovery will demonstrate significantly lower rates of smoking, higher intake of fruit and vegetables, and higher levels of physical activity. Recruitment for the study is currently underway. The study is funded by a competitive research grant from the Cancer Institute, NSW. The University of Wollongong Human Research Ethics Committee (HE13/365) has approved the research trial, which is registered with the Australian New Zealand Clinical Trials Registry (ACTRN12615000165583).

## Methods/Design

### Study setting

The research program is being conducted at four residential alcohol and other substance abuse treatment programs: The Salvation Army William Booth House (102 beds, including 82 for males and 20 for females), The Salvation Army Blue Mountains Recovery Services (22 beds for males), The Salvation Army Canberra Recovery Services (44 beds, including 36 for males and 8 for females), and The Salvation Army Dooralong Transformation Centre (125 beds, including 85 for males and 40 for females). The treatment program across each of these sites is up to 10-months in length and is operated in the form of a modified therapeutic community. The Bridge Program aims to provide a whole of life, person-centred and coordinated care approach to recovery. Its incorporates group work, case management, one to one support, spiritual support, health care, chapel services, recreational and social activities, family involvement and employment training. The program uses a range of therapeutic approaches including motivational enhancement strategies, 12 Step Model of Recovery, Cognitive Behavioural Therapy, Case Management and Vocational Education and Training. Previous research has described these programs and examined the characteristics of people accessing these services (e.g. [4,25-28]).

### Study design

It is generally preferable to examine the effectiveness of an intervention where randomisation occurs at the participant level. However, other methods of randomisation should be used where there is the potential for contamination [29]. As the current study is being delivered within a residential group based setting, where there are high levels of interaction between participants, the likelihood of contamination is extremely high. Additionally, staff members at each of the sites will be involved in co-facilitating Healthy Recovery, making them ineligible to work with controls. Due to the small number of research sites, a cluster randomised controlled trial was not appropriate. For this reason, the proposed study will be conducted as a prospective stepped-wedge cluster randomised trial, where randomisation will occur at the service level. Stepped-wedge designs are increasingly being utilised in the evaluation of interventions within routine care [29] and are recommended where there are limited numbers of clusters [30,31].

At each step of the study design, a presentation will be made to the participants at each of the Salvation Army programs asking for participants to join the study. Participants who are interested in being involved in the study will be asked to complete a checklist confirming their eligibility to participate. The research assistant providing this presentation and supervising the completion of the eligibility checklist will be blind to the randomization sequence, and in the first and final steps will be blind to both the randomization sequence and the stepped wedge study design (i.e. different research assistants will provide these presentations to ensure blindness to the stepped wedge design). The randomization schedule will be kept centrally, with the blinded research assistant not being made aware of the randomization schedule until all participants at each site have confirmed their eligibility.

The randomization procedures will be managed independently at the Clinical Research Design, IT, and Statistical Support Unit, University of Newcastle, NSW. Using a stepped-wedge design, each residential substance service will begin the study as a control site, providing treatment as usual to participants (Control). Sites will then progressively commence Healthy Recovery and will begin contributing to the intervention arm of the study in a stepped fashion (Treatment; see Figure 1). Independent statisticians will randomly generate the order of the sites. CONSORT procedures will be followed including using an intention to treat analysis [32].

**Figure 1 Fig1:**
[figure not shown]
Stepped wedge randomised controlled study design. Notes. Participants in the control condition will complete treatment as usual. Participants in the treatment condition will complete Health Recovery. The order of sites will be randomly allocated.

### Participants

All participants will be attending The Salvation Army residential programs. It is expected that over the course of the study approximately 140 people will be recruited. Previous surveys of people attending The Australian Salvation Army Recovery Service Centres indicated that on average participants are 36.97 years of age [SD = 10.65; 25]. On average, alcohol is the most commonly reported primary substance of abuse (54.2%), followed by amphetamines (13.8%), cannabis (12.0%), heroin and other opiates (9.7%) and others (1.8%). All participants will complete informed written consent and all participants will be over the age of 18.

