### Data analysis

#### Power analysis

The primary outcome is number of cigarettes/day at 8 weeks follow-up. Unpublished pilot data suggests this has a SD of 12 cigarettes/day. Assuming a baseline/follow-up correlation of 0.25 we would need a sample of 85 before and 85 after intervention to give the study 80% power to detect a 5 cigarette/day intervention effect at a 5% significance level. We have added another 15% to allow for non-parametric distribution of the data, i.e. 98 people before and after. To account for loss to follow-up we have added another 40% (based on previous RCTs conducted by the researchers), providing a sample of about 140 people who will complete before and after measures.

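### The sample-size calculation leads to about 140 people per condition, but the protocol treats 140 as the whole study; at that total, power allowing for loss is about 50–58%, not 80%

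*Protocol article*

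**What the plan says.** The Power analysis sets the endpoint ("The primary outcome is number of cigarettes/day at 8 weeks follow-up"), the spread ("Unpublished pilot data suggests this has a SD of 12 cigarettes/day") and the correlation ("Assuming a baseline/follow-up correlation of 0.25"). It concludes that "we would need a sample of 85 before and 85 after intervention" gives "80% power to detect a 5 cigarette/day intervention effect" at the 5% level. A 15% addition for non-normal data gives "i.e. 98 people before and after". A further 40% for loss to follow-up is then described as "providing a sample of about 140 people who will complete before and after measures".

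The Participants section gives the enrolment for the study as a whole: "It is expected that over the course of the study approximately 140 people will be recruited".

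The Analysis plan uses before/after as the name of the main predictor, which switches at a different time in each centre and carries the intervention effect. Baseline cigarettes/day enters separately as a covariate.

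**The concern.** The calculation starts from 85 in one condition and 85 in the other, and no later step adds the two together. A number derived per condition therefore ends as a number for the whole study. The expected enrolment of 140 is below even the 170 evaluable people that the calculation requires before any allowance for non-normality or loss, so the conflict does not depend on how the 40% is read.

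The 80% power statement for the primary outcome does not hold at the stated enrolment. A null result could then be read as evidence against the intervention when the trial had roughly even odds of detecting the effect it was designed for.

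The closing phrase of the Power analysis adds a second problem. It says that 140 people will complete the measures, although 140 is the figure after inflation for people who will not.

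**Working it through.** **Inputs (Power analysis):** SD 12; baseline/follow-up correlation 0.25; difference 5; power 80%; significance level 5%. Sidedness is not stated; two-sided reproduces the protocol's figure.

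**1. Reproducing the 85.** Two independent groups, adjusted for baseline:

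- Residual SD = 12 × √(1 − 0.25²) = 11.62
- n per group = 2 × [11.62 × (1.960 + 0.842) / 5]² = 84.8, so 85

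This matches exactly. Other formulas with the same inputs do not:

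| Formula | n |
|---|---|
| Two groups, baseline-adjusted, two-sided | **85 per group** |
| Two groups, unadjusted | 91 per group |
| Two groups, change score | 136 per group |
| Two groups, baseline-adjusted, one-sided | 67 per group |
| Same people measured under both conditions (paired): 2 × (1 − 0.25) × (12 × 2.802 / 5)² | 67.8, so 68 people |

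The 85 is therefore a per-condition number, in line with the role of before/after in the Analysis plan.

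**2. Following the inflation.**

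- 85 × 1.15 = 97.75, so 98 per condition
- 98 × 1.4 = 137.2, about 140 per condition
- Total: 2 × 137.2 = 274.4 (about 275), or 2 × 140 = 280

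**3. Power if 140 is the total, split 70 and 70.** Power = Φ(5 / SE − 1.96), with SE = 11.62 × √(2/n).

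| Loss assumption | n per condition | SE | Power | Power if the 15% allowance is used up (n/1.15) |
|---|---|---|---|---|
| None | 70 | 1.96 | 72% | 66% |
| Protocol's 1.4 factor undone (70/1.4) | 50 | 2.32 | 58% | 52% |
| 40% lost (70 × 0.6) | 42 | 2.54 | 50% | 45% |

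**4. Difference detectable with 80% power.**

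- 50 per condition: 5 × √(84.8/50) = 6.5 cigarettes/day
- 42 per condition: 5 × √(84.8/42) = 7.1 cigarettes/day

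**5. What a total of 280 would give.**

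- With the 1.4 factor undone, 100 per condition: power 86%, or 81% with the 15% allowance used up.
- With 40% actually lost, 84 per condition: power 79.6%, or 74% with the allowance used up.
- To keep 98 per condition after losing 40%: 98/0.6 = 163.3, so 164 per condition, about 328 in total.

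**The case against.** The best defence of 140 as a total is that the same people supply both the before and the after data; the words about completing before and after measures can be read that way. The stated inputs then give 68, not 85. The 68 assumes the same SD under both conditions, but only one SD is given. The study design also places participants in a control or a treatment condition, and the Analysis plan adjusts for baseline instead of using it as the comparator. If the words mean only each person's baseline and 8-week assessments, the 140 people still divide between two conditions. This defence fails, though the phrase probably explains how the slip arose.

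Four cautions do stand:

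- A reader might take 50% as the single answer. The protocol applies its 40% as a multiplier of 1.4, and undoing that gives 58%. A range is the honest statement.
- A reader might infer that the two sections print different numbers. They do not: both say about 140. The error arises within the Power analysis, and the Participants section carries it forward.
- A reader might infer that recruitment will stop at half the required size. The Participants section states an expectation, not a cap or stopping rule, and all residents are to be approached.
- A reader might want to add the further loss of precision from the centre and time terms. Its size depends on the layout and the cluster-period sizes, which the available text does not give, so no figure is put on it here.

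**Conclusion.** The point holds. The calculation reproduces exactly as a per-condition calculation and implies about 275–280 people recruited, while the protocol expects about 140. At 140 in total, power for 5 cigarettes/day allowing for loss is about 50–58%, or about 45–52% if the non-normality allowance is really needed. Even with no loss it is 72%, so the stated 80% is not reached under any of these assumptions.

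The figures assume an equal split between conditions, a two-sided 5% test and the protocol's own baseline-adjusted two-group formula. Unequal numbers per condition would lower them. The documents support a wrong power statement at the stated enrolment; they do not support a claim that enrolment is capped there.

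**What to change.** In the Power analysis, state that 85, 98 and about 140 are numbers per condition, and describe 140 as the number to be recruited, not the number who will complete the measures. Then choose one of two courses:

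- **Keep about 140 in total.** Leave the Participants section as it is and restate the power (about 50–58%) or the detectable difference (about 6.5–7.1 cigarettes/day) for about 42–50 completers per condition, naming the loss assumption used. This costs only text, but the 80% claim goes.
- **If about 280 in total was intended,** say so in both sections. Recruitment is already under way at four sites, so doubling enrolment affects time, staffing and budget and is not just a wording change. The text should also say whether 40% is a multiplier or the share expected to be lost; on the second reading, keeping 98 per condition needs about 328 in total.

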### Inclusion and exclusion criteria

All participants attending the residential program will be approached to participate in the study. Exclusion criteria have been kept to a minimum to ensure that the study can examine the effectiveness of using Healthy Recovery within a ‘real world’ setting. Participants will only be excluded from the study if: i) the person is a non-smoker, or ii) the person does not expect to be a client of the facility for the duration of the 5-week program (e.g. they are scheduled to complete the program).

### Interventions

#### Treatment condition (Healthy Recovery)

In addition to completing treatment as usual, participants in the Treatment Condition will complete Healthy Recovery. Healthy Recovery is an 8-session group based healthy lifestyle intervention that was developed for people attending residential substance abuse treatment. It is delivered over a 5-week period, with two groups being conducted each week for the first 3-weeks, and then 1 group a week conducted during the next two weeks. The first group session is completed over 90 minutes, with subsequent group sessions completed over 60 minutes. Healthy Recovery focuses on helping participants to reduce their smoking, increase their intake and variety of fruit and vegetables, and increase their level of physical activity. The intervention involves a combination of health focused psycho-education, goal setting, monitoring, motivational interviewing, and cognitive behavioural therapy. Participants are provided with pedometers to monitor their steps and these are used as a motivational tool for participants. Contingency management is also used to promote reductions in smoking. Participants will have an opportunity to earn up to $60 AUD over the course of the 5-week program if they are able to successfully reduce their smoking. Contingency management payments will be based on reductions from baseline expired carbon monoxide (CO) scores using a smokerlyzer (Micro Smokerlyzer®; Bedfont Technical Instruments Ltd, Kent, UK). In weeks 2 and 3 participants will have an opportunity to earn $5 AUD for any reductions in their CO score, $7 for halving their CO score and $15 for demonstrating that they have quit smoking. In weeks 4 and 5 participants are only rewarded for halving their CO score or quitting smoking. If smoking at least 10 cigarettes per day, participants are recommended to commence nicotine replacement therapy (NRT). If required, the NRT will be prescribed to participants by the general practitioner that attends the treatment program. Costs associated with NRT are subsidised under the Australian Pharmaceutical Benefits Scheme. The group sessions will be co-facilitated by a Salvation Army drug and alcohol worker and a member of the research team (i.e. Intern Psychologist or Clinical Psychologist). To track adherence to the intervention, group attendance logs are maintained (participants are trained to complete these logs during groups sessions). Participants are also asked to log their health behaviours each day onto a worksheet (i.e. number of cigarettes, servings of fruit and vegetables, steps walked, minutes of exercise). These worksheets are photocopied by the research staff and kept to monitor adherence.
